### Measurements

Outcome measures are obtained at baseline, 4 and 12 months. These are collected by self-administered questionnaires, blood sampling and anthropometry. Diabetes specific distress is assessed by the Problem Areas In Diabetes scale (PAID) [24,25] and self-efficacy by the Confidence In Diabetes Self-care questionnaire (CIDS) [26] adjusted for T2DM. Patient treatment satisfaction is assessed by the Diabetes Treatment Satisfaction Questionnaire (DTSQ) [27], physical activity is assessed by the short International Physical Activity Questionnaire (IPAQ-7) [28], health status and cost utility are assessed with the Euroqol-5D [29-31]. Status of depression is assessed at baseline and at 12 months using the Patient Health Questionnaire-9 (PHQ-9) [32], Demographic variables on age, gender, diabetes duration, marital status and level of education are assessed at baseline by means of a self-administered questionnaire. Glycaemic control is measured by HbA1c-level. Furthermore, BMI and blood-pressure are measured. Participants are asked to register occurrence of hypoglycaemia in care-diaries. Costs of direct health care and indirect non-healthcare will be inventoried in cost-diaries and recorded in 3-monthly intervals. Table 1 summarizes the measures and their timing.

**Table 1 T1:** Study measures

**Measures**	**Baseline**	**2 months**	**3 months**	**4 months**	**6 months**	**9 months**	**12 months**

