### Sample size

The proposed trial is designed to detect a clinically relevant change of self-monitoring of glucose on diabetes specific emotional distress and self-efficacy. No consensus exists about minimal important differences (MID) of diabetes specific distress measured with the PAID and self-efficacy measured with the CIDS. Therefore we set the MID at half a standard deviation [35]. In diabetes patients the standard deviation (SD) of PAID (scores transformed to 0–100) was 20 points [25]. Using a bonferroni correction based on two primary hypotheses with α 0.025 and β 0.15, a sample size of 86 per group is needed to find a difference of 10 points (0.5 SD). Information on the SD of the CIDS is not yet available for T2DM patients. For type 1 diabetes patients the SD of CIDS (scores transformed to 0–100) was 12 points [26]. To detect a decrease of 6 points (0.5 SD), while correcting according to bonferroni based on two primary hypotheses with α 0.025 and β 0.15 a sample size of 86 per group is needed. Taking into account different effects in different treatment groups (SU or non-SU) pre-stratification by treatment will double the sample size. Assuming a 15% drop-out rate, a total of 600 T2DM patients with HbA1c ≥ 7.0% are needed in the study. In addition, with a total of 600 patients it is expected to have sufficient power to detect a clinically relevant decrease of 0.5% in HbA1c.

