### Analyses

On the basis of an intention-to-treat analysis, differences between the intervention groups and usual care group are calculated with 95% confidence intervals. In addition per protocol analyses will be performed. The subgroups SU and non-SU will be analysed separately for all outcome measures. In case there is no effect modification by treatment the data of both subgroups will be pooled. If there are any relevant differences in baseline measurements between the 3 arms, we will adjust the outcomes for these factors (i.e. age, gender, ethnicity, status of depression, diabetes duration, marital status, level of education). Linear and logistic regression will be used to determine the effect of the intervention on each of the outcome measurements. The effect of the intervention will be estimated for sub-groups defined by duration of diabetes, socio-economic status, perceived social support and perceived severity of diabetes, glycaemic control and self-monitoring frequency in order to gain a better understanding as to who benefits most from the intervention. Analyses of moderators and mediators will be performed for the process-evaluation.

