### Economic analyses

For the economic evaluation from both the societal and the health insurer perspective all costs related to diabetes, and diabetic complications are considered relevant. Costs of the intervention (SMBG or SMUG, visits to the GP, medical specialists, therapists, dieticians and hospitalization) are considered direct healthcare costs. The costs of i.e. absence from paid and unpaid work are considered indirect healthcare costs. Differences in mean costs between the groups will be presented with 95% confidence intervals. An incremental cost-effectiveness ratio (ICER) will be given both for PAID and CIDS by dividing the incremental mean costs by the incremental mean reduction in PAID or CIDS score. A cost utility ratio will estimate the incremental costs per Quality Adjusted Life Year gained for the study period. Cost-effectiveness planes and acceptability curves will be presented and 95% confidence intervals will be estimated for the ICERs.

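### No section commits to adjusting the incremental QALY for baseline EQ-5D, and the only adjustment rule waits for observed imbalance, so precision may be lost in a secondary economic outcome

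*Protocol article*

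**What the plan says.** The Measurements section makes EQ-5D the source of the utilities: "health status and cost utility are assessed with the Euroqol-5D". On timing it says "Outcome measures are obtained at baseline, 4 and 12 months", and the EQ-5D row of Table 1 agrees.

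The Economic analyses section then commits to a cost-utility result: "A cost utility ratio will estimate the incremental costs per Quality Adjusted Life Year gained for the study period". It promises cost-effectiveness planes and acceptability curves. It gives no formula for the QALY, no model and no covariate. For the other two ratios it is more specific: they are formed "by dividing the incremental mean costs by the incremental mean reduction in PAID or CIDS score", which at least refers to change over time.

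The only covariate rule is in the Analyses section: "If there are any relevant differences in baseline measurements between the 3 arms, we will adjust the outcomes for these factors". The factors given in brackets are "i.e. age, gender, ethnicity, status of depression, diabetes duration, marital status, level of education". EQ-5D is not among them.

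**The concern.** Whether baseline utility enters the QALY analysis is left to a rule that depends on what the baseline table shows. The rule sets no threshold for a relevant difference. A chance difference of about one standard error in mean EQ-5D would not stand out in a baseline table, yet it passes into an unadjusted QALY difference. It does so partly because baseline utility is normally a component of the QALY itself, and mainly because later utilities correlate with it.

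At stake are the precision of the incremental QALY and the sharpness of the acceptability curve. The denominator of a cost-utility ratio may be a small difference, so the ratio can be sensitive to modest shifts. The baseline value that would remove much of this noise is already being collected.

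**Working it through.** **The plan's own figures.** The article gives no QALY figure to reproduce. Its sample size does reproduce: "Using a bonferroni correction based on two primary hypotheses with α 0.025 and β 0.15, a sample size of 86 per group is needed". With a difference of 10 and SD 20, 2 × (2.2414 + 1.0364)² / 0.5² = 85.95, so 86. Two strata and three arms give 516; 516 / 0.85 = 607 and 516 × 1.15 = 593, either side of the stated 600. None of this depends on the QALY analysis.

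**Inputs for the illustration.**
- From the article: EQ-5D at 0, 4 and 12 months; 200 per arm less 15% drop-out, so 170 completers per arm.
- Assumed, not in the article: QALY as a trapezoidal area under the curve; EQ-5D SD 0.20, equal at all visits; equal correlation r between any two visits, from 0.3 to 0.7.

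**Step 1, weights.** The interval from 0 to 4 months is 4/12 year and that from 4 to 12 months is 8/12 year. Half of each interval goes to each end, so the weights are 2/12 = 1/6 (baseline), 2/12 + 4/12 = 1/2 (4 months) and 4/12 = 1/3 (12 months).

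**Step 2, variance of the QALY in units of SD².** The squared weights sum to 1/36 + 1/4 + 1/9 = 0.389, so the variance factor is V = 0.389 + 0.611r.

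**Step 3, slope of the QALY on baseline utility.** b = 1/6 + (5/6)r.

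**Step 4, share of variance removed by adjustment.** R² = b²/V, and the ratio of adjusted to unadjusted SE is √(1 − R²).

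**Step 5, a one-SE chance baseline difference.** 0.20 × √(2/170) = 0.0217. It shifts the unadjusted QALY difference by 0.0217 × b.

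| r | V | b | R² | SE ratio | SE cut | SE unadjusted → adjusted | Shift |
|---|---|---|---|---|---|---|---|
| 0.3 | 0.572 | 0.417 | 0.303 | 0.835 | 17% | 0.016 → 0.014 | 0.009 |
| 0.5 | 0.694 | 0.583 | 0.490 | 0.714 | 29% | 0.018 → 0.013 | 0.013 |
| 0.7 | 0.817 | 0.750 | 0.689 | 0.558 | 44% | 0.020 → 0.011 | 0.016 |

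The unadjusted SE is 0.0217 × √V. The percentage cuts do not depend on the SD; the absolute SEs and shifts scale with it. At r = 0.5 the gain equals that from 1/(1 − 0.490) = 1.96 times as many patients for this one comparison.

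**Step 6, how much is mechanical.** The direct part of the shift is 0.0217 × 1/6 = 0.0036, against 0.013 in total at r = 0.5, so about 29%. The rest is ordinary between-visit correlation.

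**Step 7, within strata.** The Analyses section has SU and non-SU patients analysed separately for every outcome. With equal strata (assumed), 85 per arm, the one-SE baseline difference is 0.20 × √(2/85) = 0.031 and the shift at r = 0.5 is 0.031 × 0.583 = 0.018.

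**Step 8, if the QALY were a change from baseline.** The baseline weight becomes 1/6 − 1 = −5/6 and the slope −(5/6)(1 − r), so the shift changes sign. The variance factor becomes V − 2b + 1, which is 0.739, 0.528 and 0.317. The adjusted variance factor V − b² is the same under either definition: 0.399, 0.354 and 0.254. The SE cut is then 1 − √(0.399/0.739) = 27%, 1 − √(0.354/0.528) = 18% and 1 − √(0.254/0.317) = 10%. Adjustment still helps, and it gives the same estimate under either definition.

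**The case against.** The strongest reply is that this is a condensed journal article. The QALY formula and the covariates of its model commonly belong in a full protocol or an economic analysis plan, neither of which is shown. That stands for the formula, and no fault is found in its absence. It does not fully answer the point on adjustment, because the article does state a rule and that rule is triggered by observed imbalance.

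A second reply is that the rule may cover EQ-5D. It speaks of baseline measurements in general, EQ-5D is one of them, and the bracketed list may be only illustrative: the Economic analyses section uses the same abbreviation before absence from work, where an example is evidently meant. This is a fair reading. Even so, adjustment would happen only after someone judged a difference relevant, so smaller chance differences would stay in and the precision gain would be lost.

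A third reply is that most of the shift is ordinary correlation, as for any follow-up score, and that the illustrated 0.013 at r = 0.5 lies within one unadjusted SE of 0.018. Both statements are right, and they limit the weight of the point.

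A reader might go further and infer that the plan is to compare raw QALY means, or that baseline EQ-5D is deliberately left out. The documents do not support this. The cost-utility sentence fixes no estimator, and the wording about incremental means concerns only the PAID and CIDS ratios. A reader might also infer bias in favour of an arm that starts higher. Under randomisation the unadjusted difference is unbiased and its standard error already includes chance baseline imbalance. The direction of any shift also depends on a QALY definition that the article does not give.

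**Conclusion.** The point holds as a low-priority improvement. No part of the article commits to adjusting the incremental QALY for baseline EQ-5D, and its one adjustment rule is conditional on observed imbalance with a factor list that omits EQ-5D. If the QALY difference goes unadjusted, it remains valid on average but less precise than the collected data allow, and it carries chance differences in baseline utility.

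The size is a 17% to 44% cut in the standard error for correlations of 0.3 to 0.7. This rests on an assumed trapezoidal QALY, equal variances and equal between-visit correlation. Under a change-from-baseline definition the cut would be 10% to 27%. The absolute shifts also rest on an assumed EQ-5D SD of 0.20. Neither primary outcome nor the sample size is affected.

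**What to change.** Add one sentence to Economic analyses: the incremental QALY is estimated by regression of the 12-month QALY on arm, baseline EQ-5D utility and SU stratum, regardless of any observed baseline imbalance, and this adjusted difference is used in the cost-utility ratio, its plane and its acceptability curve. Where SU and non-SU patients are analysed separately, the stratum term drops out and the baseline term stays. The method chosen for joint uncertainty in costs and effects should be applied to the adjusted difference.

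This adds no patients, visits or questionnaires, because baseline EQ-5D is already scheduled for all participants. If a full protocol or economic analysis plan already says this, a reference to it is enough.

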## Discussion

This article presents a detailed description of a RCT, designed to explore the effectiveness of SMBG and SMUG on diabetes specific emotional distress and self-efficacy in non-insulin dependent T2DM patients. The proposed trial is sufficiently powered and, to the best of our knowledge, the first to allow for conclusions on the effect of self-monitoring of glucose on both diabetes specific emotional distress and glycaemic control in a large sample. In addition, due to a pre-stratification in oral treatments likely to cause hypoglycaemia or not, a possible interaction with type of treatment can be discovered. With the use of a theoretical model as a base for our hypothesis the evaluation of processes theoretically underlying the (in)effectiveness of our trial will be allowed as well. Therefore, this trial will make an important contribution to the evidence of self-monitoring in non-insulin requiring patients with T2DM.

Franciosi et al. [36] reported that a self-monitoring frequency of more than 1 measurement a day was related with the development of diabetes related distress in T2DM patients not using insulin. Unfortunately, mastering a new skill is coupled with practicing and thus a relatively high frequency. By offering participants in the intervention groups a training in self-monitoring, a control visit and a flowchart with instructions when to perform and how to interpret self-monitoring we believe that a 2 months period should be sufficient to familiarize with the self-monitoring skills considered necessary. In addition, development of diabetes-related distress caused by a high monitoring frequency is targeted by giving the participants the opportunity to independently adjust the prescribed self-monitoring frequency to one 'they feel comfortable with' starting two months after baseline.

As glycaemic control is an important issue in diabetes care most research regarding self-monitoring has focused on clinically relevant changes in HbA1c [16,37-40]. This trial primarily focuses on the effect of self-monitoring on diabetes specific distress and is additionally sufficiently powered to detect a clinically relevant decrease of 0.5% in HbA1c.

This trial will deliver important insights in the effects of self-monitoring of glucose in T2DM patients not using insulin on diabetes related distress and self-efficacy and the role of possible barriers and facilitators underlying its (in)effectiveness.

## Abbreviations

BMI: Body Mass Index; CIDS: Confidence In Diabetes Self-care questionnaire; DTSQ: Diabetes Treatment Satisfaction Questionnaire; GP: General Practitioner; ICER: Incremental Cost-Effectiveness Ratio; IPAQ-7: short International Physical Activity Questionnaire; IPQ-R: Revised Illness Perception Questionnaire; MDQ: Multidimensional Diabetes Questionnaire; MID: Minimal Important Difference; PAID: Problem Areas In Distress scale; PHQ-9: Patient Health Questionnaire; RCT: Randomized Controlled Trial; SMBG: Self-Monitoring of Blood Glucose; SMUG: Self-Monitoring of Urine Glucose; SU: Sulphonyl-Urea or Glinides; T2DM: Type 2 Diabetes Mellitus.
